#### Complexity science measures

Complexity Science Measures (Table 4) will be collected at time points as indicated. We will ask staff to report their experience over the last month; this time frame was chosen to capture the usual monthly cycle of meetings and events that may influence interactions. Although not all staff will have participated in CONNECT, we expect a system effect and, thus, all staff members should perceive changes. Further, we established adequate reliability at the organizational level using ICC, k, Eta-squared, and alpha coefficients on aggregated items scores.

### Fall measures

#### Fall risk factor reduction indicators

Measures chosen for this study are: a component of previous efficacy trials and fall clinical practice guidelines; found to be reliably measured by chart abstraction in previous studies [7,9]; and included in the educational components of the FALLS intervention. These indicators were previously found to be sensitive to change, and not impacted by a ceiling effect [7]. We will calculate the proportion of fallers with medical record evidence of the fall risk reduction indicator, and determine indicator counts for each resident. Timing of the risk factor reduction will be recorded as: within 48 hrs of a fall, within one month of a fall, during the six-month abstraction period. Definitions are found in Table 3.

#### Fall rate

Consistent with the MDS, we define a fall as an unintentional change in position resulting in a resident coming to rest on the ground or lower level [4] regardless of cause [2]. Recurrent falls are defined as two or more falls within the six-month study period [4]. These measures have been successfully employed in previous studies [2-4]. Due to underreporting of falls [94], data will be collected from multiple sources as shown in Table 3. We will calculate fall rates and recurrent falls as defined in the Table 3. From our previous falls study and national data, we assume a baseline fall rate of 1.5 falls/bed/year, and an average bed occupancy rate of 90-bed days/home/month. We therefore project that there will be a total of 2,160 falls in the study nursing homes over the study period. Proportion of repeat fallers and proportion of injurious falls (defined as proportion of falls resulting in injury including skin tear, hematoma, fracture, laceration, need for imaging or urgent assessment) will be measured as secondary fall endpoints.

### Blinding

Because of the nature of the intervention, it is not possible to mask the study assignment from the subjects or the research interventionists. However, the outcomes assessment of falls quality indicators will be completed by independent nurses employed by the state Quality Improvement Organization who will be blinded to study assignment. Success of blinding will be evaluated by asking these nurses to state which intervention they believe that the nursing home received.

### Analysis

The study hypotheses pertain to the cluster level of the nursing homes. Hierarchical linear modeling with Glimmix was used to account for clustering in this study. This procedure is useful when there are multi-level, nested sources of variability such as patients and staff clustering within nursing homes. The Glimmix procedure analyzes both individual and group level trajectories of change over time. Our hypotheses (H) to address the study aims and related analysis are listed below.

#### Aim 1

##### H1A

Residents in facilitates randomized to receive CONNECT + FALLS will have greater improvements in fall risk factor assessment counts from the six-month period preceding the intervention (baseline) to the six-month period after the intervention (follow-up), compared to similar residents in facilities receiving FALLS alone.

##### H1B

Residents in facilities randomized to receive CONNECT + FALLS will have greater improvements in fall risk factor intervention counts from the six-month period preceding the intervention (baseline) to the six-month period after the intervention (follow-up), compared to similar residents in facilities receiving FALLS alone.

As the dependent variables for H1a and H1b are counts, we will use PROC GLIMMIX to estimate the models. A significant negative coefficient will indicate that the intervention reduced fall rates. As is standard practice with Poisson models, we will test for over dispersion in initial analyses and employ a negative-binomial model if over dispersion is present.

#### Aim 2

##### H2A

Residents in facilities randomized to receive CONNECT + FALLS will have lower fall rates, compared to residents in facilities receiving FALLS alone.

##### H2B

Residents in facilities randomized to receive CONNECT + FALLS will have a lower probability of recurrent falls during the six months post-intervention, compared to similar residents in facilities receiving FALLS alone.

##### H2C

Intervention-related improvements in fall rates and injurious falls will be mediated by improvements in fall-related process measures.

The dependent variables for H2a and H2b will consist of one Poisson distributed outcome (fall rates), and one dichotomous outcome (the probability of a recurrent fall). For fall rates, we will use PROC GLIMMIX to re-estimate the model with fall rates dependent and intervention group, time, and relevant covariates as predictors, using the same analysis as for Aim 1. To test H2c, we will add the process measures (from Aim 1) to the models for H2a and H2b as time-changing predictors. We will use bootstrap methods [95] to test significance of these indirect effects.

#### Aim 3

##### H3A

Staff in facilities randomized to receive CONNECT + FALLS will report significantly greater improvement from baseline immediately and three months after the intervention than staff in facilities receiving FALLS alone on complexity science measures of: communication openness, accuracy and timeliness; participation in decision making; relational coordination; psychological safety; and safety culture.

For these outcomes, we will use PROC MIXED to estimate a mixed model to estimates the effect of the intervention on each outcome averaged over time.

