CONNECT is a multi-component intervention that helps staff: learn new strategies to improve day-to-day interactions; establish relationship networks for creative problem solving; and sustain newly acquired interaction behaviors through mentorship. Complexity science and empirical research suggest that interaction patterns determine information flow, knowledge transfer, and capacity to monitor behaviors in healthcare settings [16,18,30]. In a preliminary test of CONNECT, we found support for the hypothesis that the intervention would improve staff interactions and reduce falls [31]. We propose that CONNECT, when combined with a content focused falls QI program (FALLS), will result in better resident outcomes when compared to FALLS alone. We chose falls for this test of CONNECT because: falls rates are high in nursing homes [32,33]; accepted practice guidelines and fall prevention programs exist [34-37]; and there is ample evidence from efficacy trials that multi-factorial risk reduction interventions reduce fall rates [3-5,13,38].

The study aims are to:

1. Compare the impact of the CONNECT intervention plus a falls reduction QI intervention (CONNECT + FALLS) to the falls reduction QI intervention alone (FALLS) on fall-related process measures in nursing home residents.

2. Compare the impact of CONNECT + FALLS to FALLS alone on fall-rates in nursing home residents, and determine whether these are mediated by the change in fall-related process measures.

3. Compare the impact of CONNECT + FALLS to FALLS alone on complexity science measures as reported by nursing home staff and determine whether these mediate the impact on fall-related process measures and fall rates.

To complete these aims we will use a cluster randomized, controlled trial design with the facility-level change in fall and complexity science measures as the primary outcomes. Because the CONNECT and FALLS interventions both encourage facility-wide change in staff behavior, randomization will occur at the facility level and subjects (nursing home staff and residents) are clustered within homes.

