#### Staff sample

Staff members who work with residents in a clinical capacity (e.g., registered nurses, licensed practice nurses, NAs, social workers, dietary, activities, physical and occupational therapists) on skilled and assisted living units will be eligible to participate. The only exclusion criterion is inability to understand English. Using current staff lists provided by the administrator, we will invite staff to participate. In our pilot studies, 80% to 84% of staff invited, participated in survey completion. Thus, we conservatively estimate that of about 960 staff members, 60% will participate in training and complete surveys for an estimated enrollment of 576 staff members. New employees will be invited to participate in CONNECT up to the fourth week of the intervention. Those joining later will be invited to enroll only to complete the cross-sectional staff interaction measures. Based on data from the 2000 U.S. Census, we project that staff racial composition will be 57% white, 39% African American, and 3% other races [71]. Our pilot studies included 34% underrepresented minority participants.

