### Statistical power

We used algorithms developed to estimate power for longitudinal models based on the formulae of Jung and Ahn [96], a type I error rate of 0.05 (two-tailed), and a 15% rate of attrition for the staff samples. Hierarchical linear modeling with SAS PROC Glimmix was used to account for clustering in this study. This procedure is useful when there are multi-level, nested sources of variability such as patient and staff clustering within nursing homes. The Glimmix procedure analyzes both individual and group level trajectories of change over time, and can be used to estimate models where persons within clusters are changing over time. Maximum cluster size was limited by the pool of resident fallers and number of staff in each facility. The power analysis algorithms used to determine cluster size take clustering at the individual level into account. In the analyses, we will treat cluster as a fixed rather than as a random effect. This approach will more adequately control on potential confounders at the level of the nursing home. With cluster analyzed as a fixed effect, inter-cluster correlations are not needed to calculate power.

For aim one, we will have 80% power to detect a 15% difference in risk factor assessment and intervention scores, which is considered to be the minimally clinically significant improvement in falls care practice. For aim two, the resident sample will provide 80% power to detect a 23% difference in the fall rate due to intervention, and a 23% difference in the probability of a recurrent fall. Because this is a real world effectiveness study, this change in fall rate is slightly smaller than that seen in a randomized controlled trial of multifactorial risk factor reduction, but still clinically meaningful. For the continuous outcomes in aim three, we will have 80% power to detect standardized differences of 0.21, a magnitude considered small in the statistical literature [97]. As we have a single primary outcome and several additional outcomes that are exploratory, we will not adjust our significance tests for multiple tests.

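### The Aim 3 model targets one time-averaged arm effect, which does not test H3A's change from baseline at two follow-ups; the fall-rate model should name arm-by-period as its test

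*Protocol article*

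**What the plan says.** **Aim 3 (Protocol article, Analysis).** H3A says that staff in CONNECT + FALLS homes will report "significantly greater improvement from baseline immediately and three months after the intervention" than staff in FALLS homes on the complexity science measures. The next sentence describes a PROC MIXED model for "the effect of the intervention on each outcome averaged over time". It names no arm-by-wave term, no contrast with baseline and no baseline adjustment. The dated survey waves are baseline, month 3 and month 6 (Methods and design; Data collection from staff).

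**Primary outcome (Background, study aims).** The trial is set up "with the facility-level change in fall and complexity science measures as the primary outcomes".

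**Fall rates (Aim 2 text under H2C).** The model has "fall rates dependent and intervention group, time, and relevant covariates as predictors" and refers back to the Aim 1 analysis. The Aim 1 text gives a Poisson or negative-binomial model but lists no terms. Falls are counted in a six-month window before baseline and another after the intervention.

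**Home effect.** The Statistical power section says nursing home will be fixed rather than random in the analyses. The Abstract describes a three-level mixed model. For Aim 3 the same section claims "80% power to detect standardized differences of 0.21".

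**The concern.** Two adjoining sentences under Aim 3 describe different quantities. The hypothesis is two differences in change, one per follow-up. The model sentence is a single difference in level, pooled over waves. One pooled number cannot distinguish an early effect that fades from a late one that builds, although Methods and design gives immediate and sustained impact as the reason for the two follow-ups. It also merges month 3, when the combined arm has had CONNECT only, with month 6, after both programmes.

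At stake is whether the named analysis can be fitted at all under the protocol's own rule for home. If it can, the further question is whether it estimates the effect the trial was sized for. The fall-rate predictor list raises a related but weaker question, because the data are a before and an after window and no term is named that compares the arms in their change between them.

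**Working it through.** **Inputs from the protocol.** 16 homes, two arms; three staff waves; two fall windows; "an estimated enrollment of 576 staff members"; "a 15% rate of attrition for the staff samples"; two-sided 5% error, 80% power; 0.21 SD for Aim 3; 23% for the fall rate; 2,160 projected falls.

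**Assumptions.** Equal allocation, so 288 staff per arm and 288 × 0.85 ≈ 245 after attrition. Exchangeable within-person correlation r, which the protocol does not give; 0.3 to 0.8 is shown. One sentence on the surveys mentions four completions; the three dated waves are used.

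**1. The plan's 0.21 SD.** For a single-wave comparison the detectable difference is (1.960 + 0.842) × √(2/n):
- n = 288: 0.233 SD
- n = 245: 0.253 SD

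Reaching 0.21 with 245 per arm needs a variance factor of (0.21/0.253)² ≈ 0.69.
- Three-wave mean: (1 + 2r)/3 = 0.69 at r ≈ 0.53.
- Mean follow-up minus baseline: 1.5(1 − r) = 0.69 at r ≈ 0.54.

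Both contrasts reach 0.21 at nearly the same r, so the figure does not reveal which one was powered.

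**2. Home fixed.** The design has 16 home columns plus 2 wave columns: rank 18. The arm column is the sum of the home columns in that arm, so adding it leaves rank 18 and its coefficient is not estimable. Adding arm × wave instead gives rank 20, so both change contrasts are estimable. With two fall windows the same reasoning gives 16 + 1 = 17, still 17 with arm, and 18 with arm × period.

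**3. Home random, baseline among the averaged waves.** Take a true effect of 0 at baseline and 0.21 SD at each follow-up. The average is (0 + 0.21 + 0.21)/3 = 0.14 SD. A persistent difference of b SD between arms shifts this average by b; it shifts the difference in change by (b − b) = 0.

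Power with 245 per arm:

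| Contrast | Effect | Variance factor | r = 0.3 | r = 0.5 | r = 0.8 |
|---|---|---|---|---|---|
| Mean of three waves | 0.14 | (1 + 2r)/3 | 56.4% | 47.5% | 38.4% |
| Mean follow-up minus baseline | 0.21 | 1.5(1 − r) | 62.1% | 76.5% | 98.9% |
| Mean follow-up, baseline as covariate | 0.21 | (1 + r)/2 − r² | 87.4% | 90.8% | 99.5% |

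These ignore clustering by home, so they are optimistic and serve only to compare contrasts.

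**4. Home random, follow-ups only.** The average is (0.21 + 0.21)/2 = 0.21 SD: no dilution when the effect is equal at both waves. Baseline is still unadjusted, and the two times are still not tested separately.

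**5. Fall rates, home not fixed.** The 2,160 falls reproduce as 16 homes × 90 occupied beds × 1.5 falls per bed-year for one year, that is, two six-month windows. Per arm and window: 2,160/4 = 540. With a 23% reduction after the intervention only, the treated arm has 540 × 0.77 = 415.8 falls in the second window.
- Group main effect over both windows: (540 + 415.8)/(540 + 540) = 0.885, an 11.5% reduction. Averaging on the log scale gives 0.77^0.5 = 0.877, about 12%. For 0.885 the standard error is √(1/955.8 + 1/1,080) = 0.0444 and Poisson power is 79%.
- Arm × period: rate ratio 0.77, standard error √(3/540 + 1/415.8) = 0.0892, power 83%.

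The power gap is small; the main harm is an estimate about half its true size. Overdispersion would lower both powers.

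**The case against.** The strongest defence is that this is a condensed article and the sentence is short. The average could be meant over the two follow-ups only, or even over the two changes from baseline. The Analysis section speaks of trajectories of change, and with home fixed the only estimable intervention effect is within-home change, which is what H3A asks for. This has force against the size of the harm. It does not rescue the sentence: no change contrast is named, and even an average of two changes leaves H3A's two time-specific claims untested.

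Four stronger readings are tempting and are not supported.

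- **That the fall-rate model is also declared a time average, against its hypothesis.** The averaging wording occurs only under Aim 3. H2A claims only lower rates, and H2B concerns the post-intervention window. The case for change rests on the Background sentence and H2C's reference to improvements. The pointer to Aim 1, whose hypotheses are about change, may mean that an interaction is intended.
- **That dilution, baseline imbalance and non-estimability all apply together.** They cannot. With home fixed, stable differences between homes are absorbed and no 0.14 SD estimate arises. Dilution and imbalance require home not to be fixed, and dilution also requires baseline to be in the average.
- **That month 6 is the proper test.** H3A's two times fit months 3 and 6 if counted from the end of CONNECT, and it ranks neither above the other.
- **That the 0.21 SD was computed for the wrong contrast.** Without r, this cannot be shown.

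**Conclusion.** For Aim 3 the point holds: the stated effect does not test H3A under any of these readings, and it does not match the primary outcome as change. Under the protocol's fixed-home rule, an averaged arm effect cannot be estimated; this rests on algebra and needs no assumed figures. With home random and baseline averaged in, the estimate is two thirds of the true effect (0.14 against 0.21 SD, assuming equal wave weights and equal effects at both follow-ups) and takes up any persistent difference between arms. With follow-ups only, the dilution goes under equal effects, but the lack of baseline adjustment and of separate tests remains.

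For fall rates the finding is limited to an incomplete statement: the listed predictors contain no arm-by-period term, although the data are a before and an after window. If the list were applied literally, a 23% reduction would appear as about 11.5–12% with home not fixed, and would be inestimable with home fixed.

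**What to change.** - **Aim 3.** Replace the time-averaged wording with an arm-by-wave model. Test the between-arm difference in change from baseline at month 3 and at month 6, and say whether H3A needs both. The average of these two change contrasts may be added as a summary.
- **Fall rates.** Name the arm-by-period coefficient as the tested parameter. Listing the terms once under Aim 1 would settle the cross-reference.
- **Home effect.** A model of follow-up data with baseline as covariate is an option only if home is not a fixed effect; with home fixed and follow-up data alone, arm is aliased with home.

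The first two changes cost only analysis wording, since the baseline and follow-up data are already planned. The baseline-covariate route costs more: it would mean revising the fixed-home statement and the power argument built on it.

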##### H3B

Improvements in fall-related process measures and fall-related outcome measures will be mediated by changes in complexity science measures.

To test H3B, we will calculate nursing home-level means on the complexity science measures, add these mean as time-changing predictors to our models (above) predicting fall-related process and outcome measures. We will use bootstrap methods [95] for testing the significance of these indirect effects.

### Statistical power

We used algorithms developed to estimate power for longitudinal models based on the formulae of Jung and Ahn [96], a type I error rate of 0.05 (two-tailed), and a 15% rate of attrition for the staff samples. Hierarchical linear modeling with SAS PROC Glimmix was used to account for clustering in this study. This procedure is useful when there are multi-level, nested sources of variability such as patient and staff clustering within nursing homes. The Glimmix procedure analyzes both individual and group level trajectories of change over time, and can be used to estimate models where persons within clusters are changing over time. Maximum cluster size was limited by the pool of resident fallers and number of staff in each facility. The power analysis algorithms used to determine cluster size take clustering at the individual level into account. In the analyses, we will treat cluster as a fixed rather than as a random effect. This approach will more adequately control on potential confounders at the level of the nursing home. With cluster analyzed as a fixed effect, inter-cluster correlations are not needed to calculate power.

For aim one, we will have 80% power to detect a 15% difference in risk factor assessment and intervention scores, which is considered to be the minimally clinically significant improvement in falls care practice. For aim two, the resident sample will provide 80% power to detect a 23% difference in the fall rate due to intervention, and a 23% difference in the probability of a recurrent fall. Because this is a real world effectiveness study, this change in fall rate is slightly smaller than that seen in a randomized controlled trial of multifactorial risk factor reduction, but still clinically meaningful. For the continuous outcomes in aim three, we will have 80% power to detect standardized differences of 0.21, a magnitude considered small in the statistical literature [97]. As we have a single primary outcome and several additional outcomes that are exploratory, we will not adjust our significance tests for multiple tests.

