**Methods/design:**

Sixteen nursing homes will be randomized to one of two study arms, CONNECT + FALLS or FALLS alone. Subjects (staff and residents) are clustered within nursing homes because the intervention addresses social processes and thus must be delivered within the social context, rather than to individuals. Nursing homes randomized to CONNECT + FALLS will receive three months of CONNECT first, followed by three months of FALLS. Nursing homes randomized to FALLS alone receive three months of FALLs QI and are offered CONNECT after data collection is completed. Complexity science measures, which reflect staff perceptions of communication, safety climate, and care quality, will be collected from staff at baseline, three months after, and six months after baseline to evaluate immediate and sustained impacts. FALLS measures including quality indicators (process measures) and fall rates will be collected for the six months prior to baseline and the six months after the end of the intervention. Analysis will use a three-level mixed model.

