## Methods and design

In this cluster randomized, blinded trial, 16 nursing homes will be randomized to one of two study arms either to receive CONNECT + FALLS or FALLS alone. Subjects are clustered within nursing homes because the intervention addresses social processes and thus must be delivered within the social context, rather than to individuals. Nursing homes randomized to CONNECT + FALLS will first complete the CONNECT protocol, after which they will receive the FALLS protocol. Nursing homes randomized to FALLS alone will be offered CONNECT following data collection. Complexity science measures, to be completed by nursing home staff, will be collected at baseline, and three and six months after baseline to evaluate the immediate and sustained impact on system parameters. FALLS measures, collected from medical record review, will be collected longitudinally for the six months prior to baseline and the six months after the end of the intervention to allow adequate fall events to accrue. A five-year timeline is planned to complete the study. This study was review and approved by the Duke University Medical Center Institutional Review Board.

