#### Resident sample

Eligibility criteria include: > 65 years of age; sustained a fall as defined by Minimum Data Set (MDS) criteria in the study period; and remained in the facility for at least 30 days after the fall event. This sampling strategy will allow us to measure fall risk factor reduction activities completed by the nursing home staff for their highest risk residents (i.e., known fallers). Previous studies suggest a fall rate of 1.5 falls/bed-year, of which 40% are recurrent fallers [32-59]. Of the approximately 1,600 residents in the study nursing homes, we estimate a resident pool of n = 1,440 unique fallers which exceeds our needed resident sample size of 800. Lists of residents who have fallen during the study period will be generated from the nursing home MDS and incident reports. A random sample of 50 unique residents from each nursing home will be selected for chart abstraction using a random number generator. Because this is a minimal risk study in which residents are not followed prospectively, we have obtained a waiver of informed consent.

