#### Measures

The measures and the time points at which these will be collected are summarized in Table 4[79,17,30-93] (Complexity Science Measures) and Table 3 (Fall-related measures). In addition, data will be collected about each nursing home, including bed size, nursing staff hours. Chain and religious affiliation will be collected from publicly available sources http://www.nhcompare.gov. Nursing staff turnover during the intervention period will be obtained from administrators. These data will be used as covariates in the multivariable outcomes analyses. All measures will be aggregated to the cluster level of the facility.

**Table 4 T4:** Complexity science measures

Concept Measured; Source	Psychometrics; Calculation
Demographics; self-report	Age, sex, job title, years in position, education, and ethnicity (collected at baseline or at enrollment into the study. Categorical measurement)

Communication patterns; all staff	Mean scores on Roberts and O'Reilly openness, accuracy scales [79] and Shortell's timeliness scale [80,81]. The scales show adequate reliability and validity in various settings [79,80,82]. In our preliminary studies scales showed reliability alphas of 0.81, 0.72 and 0.68, respectively; construct validity confirmed by factor analysis and hypothesis testing [17,30,83].

NA and LPN participation in decision making about resident care; all staff	Mean score on Anderson et al.'s [83] Participation in Decision-making Instrument (PDMI). The PDMI is established with demonstrated reliability in nursing homes [17,18,83-85] and construct validity established through factor analysis [83] and hypothesis testing [17,84,86]. Nursing home samples achieved alpha coefficients of > 0.90.

Relational Coordination; all staff	Mean scores on Gittell's [87] five-point scale on which staff will rate interactions between groups (e.g., NA to nurse, NA to dietary; nurse to MD). Three aspects are measured including: frequency of communication; high-quality communication; and supportive relationships [88,89]. Gittell [88] adapted this scale for nursing homes and achieved a one factor scale and a Chronbach's alpha 0.86. In our preliminary study, we achieved an alpha of 0.95 on a sample of nursing home staff.

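### Fitting nursing home as a fixed effect in a trial that randomises 16 homes makes arm main effects inestimable and leaves an individual-level test of change without a valid error term

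*Protocol article*

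**What the plan says.** All statements are from the protocol article.

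- **Unit of randomisation.** The Background states that "randomization will occur at the facility level and subjects (nursing home staff and residents) are clustered within homes". Methods and design gives the number: "16 nursing homes will be randomized to one of two study arms either to receive CONNECT + FALLS or FALLS alone".
- **Level of inference.** The Analysis section says "The study hypotheses pertain to the cluster level of the nursing homes". The Background names facility-level change as the primary outcome.
- **Model, first description.** The Abstract says "Analysis will use a three-level mixed model", and the Analysis section describes hierarchical modelling in GLIMMIX.
- **Model, second description.** The Statistical power section says "In the analyses, we will treat cluster as a fixed rather than as a random effect". It gives control of home-level confounders as the reason, and infers that correlations at home level can be left out of the power calculation.
- **Contrasts.** H1A, H1B and H3A are worded as greater improvement from baseline. H2B compares arms in the six months after the intervention only. The Aim 2 fall-rate model lists group, time and covariates, and names no group-by-time term.
- **Covariates.** Of home characteristics such as bed size, staffing hours, chain and religious affiliation, the Measures section says "These data will be used as covariates in the multivariable outcomes analyses". The same section says that all measures will be aggregated to the facility.
- **Sample.** "A random sample of 50 unique residents from each nursing home will be selected for chart abstraction using a random number generator". The text does not say whether this is per period. Expected staff enrolment is 576, with 15% attrition.

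**The concern.** In a cluster-randomised trial the treatment varies only between clusters. Indicators for every cluster use up exactly that information. The step meant to control home-level confounders therefore also removes the arm main effect.

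What remains is the difference between arms in change. If it is tested on individual records with only residual error (plus, for staff, a person effect), residents or staff count as independent replicates of an intervention allocated to 16 homes. Homes also change for their own reasons, and the Risks and challenges section itself raises staff and administrator turnover. Such variation would be read as treatment effect.

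At stake are whether H2B and the Aim 2 group term can be fitted at all, whether the p-values for change are valid, and whether the stated power is achievable.

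**Working it through.** **1. The plan's own power figures.** They can be approached only as individual-level calculations.
- Aim 3: 576 × 0.85 / 2 ≈ 245 staff per arm. For a standardised difference of 0.21 measured once, power is 64%; 80% needs 2 × (2.802/0.21)² ≈ 356 per arm. With 245 per arm, 80% is reached if, for example, three waves are averaged with a within-person correlation of about 0.53 and home-level variance is zero. That correlation is not stated.
- Aim 2, recurrent falls: if the 40% in the Resident sample section is the control proportion and 23% is a relative reduction, the comparison is 40% against 30.8%. With 400 per arm and no design effect, power is about 78% (423 per arm needed for 80%).

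The stated 80% is thus not confirmed exactly, but both results are close to it only when home-level variance is left out.

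**2. Estimability.** Take 16 homes, 8 per arm (assumed), and two periods.

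| Design matrix | Columns | Rank |
|---|---|---|
| Homes + period | 17 | 17 |
| Homes + period + arm | 18 | 17 |
| Post-period only: homes + arm | 17 | 16 |
| Homes + period + arm × period | 18 | 18 |

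Arm adds nothing to the home indicators, so no arm main effect is estimable; arm × period is. Covariates constant within home, such as chain status, are aliased in the same way, although the home indicators absorb their confounding.

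**3. Type I error of the individual-level arm × period test with fixed homes.** Assume repeated cross-sections with m residents per home-period, intracluster correlation ICC, and cluster autocorrelation CAC (the correlation between a home's effects in the two periods). The true variance exceeds the model variance by

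VIF = 1 + m × ICC × (1 − CAC) / (1 − ICC), and the actual error is 2 × [1 − Φ(1.96/√VIF)].

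Example: m = 50, ICC 0.05, CAC 0.8 gives VIF = 1 + 50 × 0.01/0.95 = 1.526, and an error of 2 × [1 − Φ(1.587)] = 11.3%.

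| ICC | m = 50, CAC 0.8 to 0.5 | m = 25, CAC 0.8 to 0.5 |
|---|---|---|
| 0.02 | 7.4% to 11.1% | 6.2% to 8.0% |
| 0.05 | 11.3% to 19.8% | 8.1% to 12.8% |
| 0.10 | 17.7% to 31.3% | 11.6% to 20.5% |

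Simulation (4,000 trials per setting, m = 50) gave 7-11%, 11-20% and 17-31%. A home-level test of change on 14 df stayed at 4-6%. With home-by-period variance exactly zero, the fixed-home test is also at about 5%.

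**4. Power once home-level variation in change is in the error term.** Take the stated 80% as given, so the noncentrality is 1.96 + 0.842 = 2.802. Divide it by √DE, where DE = 1 + (m − 1)ρ and ρ is the home-by-period ICC, and use a noncentral t on 14 df.

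| ρ | 50 residents: DE, power | 31 staff (490/16): DE, power |
|---|---|---|
| 0 | 1.00, 74% | 1.00, 74% |
| 0.01 | 1.49, 57% | 1.30, 63% |
| 0.02 | 1.98, 46% | 1.60, 54% |
| 0.05 | 3.45, 29% | 2.50, 38% |

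If the stated 80% instead rests on 25 residents per home-period, the same formula gives 65%, 57% and 42% at ρ = 0.01, 0.02 and 0.05.

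**The case against.** The strongest defence is that a fixed home effect is not in itself the defect. Fixed intercepts remove all stable differences in level between homes. The article also names facility-level change as primary and mentions aggregation to the facility. Home indicators, period and arm × period fitted to the 32 home-period means leave 14 residual df and give exactly the t statistic of a two-sample test on the 16 home-level changes. That analysis is valid. This stands, so a reader who infers that every arm-by-time test under this plan is invalid goes too far. But the Statistical power section plans no such analysis: the aims describe count and mixed models on residents and staff, and home-level correlation is set aside.

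A reader might also infer that the treatment term is lost for every aim. It is not. H1A, H1B and H3A concern change, and the effect averaged over time in H3A can be read as change averaged over follow-up waves. H2B clearly needs an arm main effect; H2A is ambiguous, but the terms listed for its model describe one.

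Three further limits stand.
- The error rates above do not carry over directly to the fall rate. Table 3 defines it per facility, and the plan checks for overdispersion with a negative-binomial fallback, which may absorb home-by-period variation. With an assumed home-by-period SD of 0.15 on the log scale, a Pearson-scaled fit on 14 df had a type I error of about 6%, against 22% for unscaled Poisson. The negative-binomial fit was not tested.
- The statement that "we established adequate reliability at the organizational level using ICC" is not evidence of variation in change. It gives no value and concerns the reliability of aggregated scores.
- Fixed homes with random persons is still a mixed model. The tension is with the three-level and hierarchical descriptions.

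**Conclusion.** The concern holds in this limited form. The aliasing is algebra and rests on no assumed figure: with home fixed, the H2B contrast and the Aim 2 group main effect cannot be estimated. An individual-level test of change without a home-by-period error term, which is what the aims' models together with the Statistical power section imply, is anti-conservative unless homes do not differ in change.

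The size of the inflation is illustrative. It rests on assumed ICCs of 0.02 to 0.10, an assumed autocorrelation of 0.8 to 0.5, and 25 or 50 residents per home-period, because the article leaves that open. Over these ranges the error runs from about 6% to 31%. The loss of power likewise depends on the assumed home-by-period ICC, but even at zero the 14 df alone take 80% to 74%. The article's descriptions of the model must be reconciled whichever values apply.

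**What to change.** 1. Delete the sentences in the Statistical power section that make home a fixed effect and that dispense with between-home correlation. Reconcile the Abstract, Background, Measures, Analysis and Statistical power sections on one model and one level of data.
2. In the individual-level GLIMMIX and MIXED models, fit a random home intercept and a random home-by-period effect. Test arm-by-time on between-home degrees of freedom, about 14 less the number of home-level covariates (for example Kenward-Roger). Alternatively, analyse the 16 home-level changes.
3. Keep chain affiliation, the randomisation stratum, as a covariate.
4. Say whether the 50 residents per home are per period. Restate the power for each aim with a stated ICC and 14 df.

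No design or data-collection change is needed. The cost is wider intervals and less favourable stated power.
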